**Data on Quality of Life and behavior**

The second main data source are questionnaires on quality of life and the Child Behaviour Checklist (CBCL), which are collected via mail. This will minimize loss to follow-up for this aspect of the study, as all patients and families will continue to be contacted even if they no longer attend or plan to attend medical appointments.

The KINDLR quality of life questionnaires by Ravens-Sieberer and Bullinger are a brief and flexible survey instrument that can be completed by children and adolescents as well as their parents [14–16]. The KINDLR questionnaires have been used in many studies and are characterized by high reliability, validity and user acceptance. They focus on the analysis of the following domains: physical well-being, emotional well-being, self-esteem, family, friends and school/education.

The CBCL is used to record behavioral problems, emotional abnormalities, somatic complaints and social skills of preschool-aged, school-aged children and adolescents from the parents’ perspective [17]. The survey covers the following sub-areas, known as problem scales Anxious/depressed, withdrawn/depressed, somatic complaints, social problems, thinking, (sleep) and repetition problems, attention problems, rule-breaking and aggressive behavior.

### Organization

The coordinating study center is located at the LMU University Hospital Munich and is responsible for the study protocol and the development of the CRFs, for the initiation and coordination of the study centres and the quality of the data entry. In addition, it collects quality of life data directly from families who have given their consent.

The database is located at the Institute for Medical Information Processing, Biometry, and Epidemiology (IBE) at the LMU Munich. Statistical analyses will also be performed there.

### Steering committee

A steering committee has been formed, consisting of national and international experts in the field of paediatric neurology, neuroradiology, haematology, rehabilitation medicine, intensive care medicine, and with representatives from Austria and the Netherlands to include country specific issues. The committee oversees the study, provides advice and decides on research proposals from investigators for data access.

### Ethics statement

The study has been approved by the ethics committee of the University of Munich (21–0571 and 3 amendments). Additionally, each local ethics committee has to approve the study for each study centre. PRiSMA is and will be conducted in accordance with the protocol, the Declaration of Helsinki and the principles of Good Clinical Practice.

PRiSMA is registried at the German Clinical Data Register (DRKS 00034715).

### Data management

Data are collected using a dedicated electronic data capturing system (REDCap). To comply with data protection laws, a hash value is generated from each patient’s insurance number and date of birth, which serves as a pseudonym. As the hashing procedure is non-reversible and only the pseudonym is saved, this system allows for combining a patients’ data through multiple institutions while ensuring that each centre has only access to its own data. Patients without insurance numbers will be assigned a pseudo-insurance number, which they can present at subsequent institutions.

Access to the data can be granted to interested scientists after sending in a proposal of the intended use. The decision on the proposal is made by the steering committee.

### Statistical analysis

The PRiSMA registry serves both to answer important questions and to generate new hypotheses exploratively.

Main outcome measurements are mortality, risk of recurrence, quality of life (measured via the KINDLR), behavioural and emotional function (measured via the CBCL) and neurological deficit and function (mRS, GMFCS, MACS, etc).

Continuous variables are described using the median and interquartile range or the mean and standard deviation. Categorical variables are described using relative and absolute frequencies. Event time data are described using Kaplan-Meier curves. In the presence of competing events, such as the occurrence of a recurrence and mortality without a prior recurrence, cumulative incidence curves considering both risks are used.

To identify prognostic factors, appropriate multiple regression models are conducted like linear, logistic, Cox proportional hazards or Fine and Gray model. If necessary, multiple imputation procedures for missing values have to be used.

Analyses will be performed with either SAS or R.

### Safety considerations

As the registry is purely observational, no safety issues arise.

### Current status

Start of recruitment was on 07/02/2024. Currently, 31 patients have been included in the registry (by 17 Nov 25). Up to now, 17 centres have signed the necessary documents and are eligible for patient enrolment, further study centres are being set up.

### Dissemination

Results of the study will be published in scientific journals and presented at national and international conferences. Key results will afterwards be shown on the study website (https://www.prisma-pediatricstroke.com/).

## Discussion

Our goal is to optimise diagnostics and personalise therapy in the acute and long-term phases to achieve the best possible outcomes for children and adolescents with stroke. To this end, we require a systematic database to develop appropriate diagnostic and therapeutic protocols. PRiSMA is a prospective multicentre registry for childhood stroke, recording data on acute care, long-term therapy, and health economics, while assessing the quality of life of affected children and adolescents over an extended period of time.

## Strengths

PRiSMA is the first stroke registry for children and adolescents in Germany, Austria and the Netherlands. With a German population of approximately 83 million people and additional centres in Austria and the Netherlands, it covers a large geographical area.

The registry includes children with both ischaemic and haemorrhagic stroke, the latter of which is more often characterised by severe functional limitations and higher economic costs [18]. Thanks to the PRiSMA structure, patients can be monitored over many years, and thanks to the construction of the pseudonymisation procedure developed specifically for this purpose allowing data linkage across sites, they can be monitored across many institutions in compliance with data protection regulations. Quality of life, behaviour and the impact of the stroke on future education are particularly important for children and adolescents and their families [19].

For this reason, PRiSMA has set up a special study to examine quality of life and behaviour. Data collected at regular intervals enables the needs of those affected to be identified directly and addressed more effectively. Acute stroke care has changed fundamentally in the last decade. Revascularisation procedures, such as thrombolysis and mechanical thrombectomy, have become standard practice in adult neurology and are now being used to treat children and adolescents with stroke [20–22].

However, this approach is not yet evidence-based. Therefore, PRiSMA’s ability to collect data during this era of revascularisation to assess impact on functional outcomes and collect data on complications in the acute phase of management and long-term outcomes is a significant advantage.

Thanks to the German Network Paediatric Stroke, which has been active and growing for over 10 years, the heterogeneity of the care landscape can be mapped in great detail. This is because the study includes not only university clinics, but also peripheral children’s clinics and paediatric rehabilitation clinics. Integrating the patient’s residence degree of urbanisation [23] enables potential inequalities in acute and long-term treatment for children and adolescents, depending on their location, to be identified. These criteria are an essential aspect of care research and, in the long term, could contribute to reducing inequalities and creating equal care opportunities for all children and adolescents, regardless of where they live, e.g., by facilitating access to telemedicine.

Furthermore, additional socio-economic factors, such as access to therapies, functional outcomes and quality of life, depending on parents’ level of education, can be identified. This highlights the need for an appropriate awareness campaign.

## Limitations

Currently, not all German children and adolescents who have had a stroke are covered by the registry. However, a nationwide network of >25 centres is being created across all federal states in Germany and this is set to expand with the initiation of more clinics including centres in Austria and the Netherlands.

From a statistical point of view, missing values are a very common issue in registries. To address this, we have developed a multifaceted strategy. Firstly, we have focused on including only items that are routinely collected by physicians treating paediatric stroke patients. Secondly, data will be curated throughout the study and missing values will be queried. Finally, multiple imputation techniques will be used to address any remaining missing data in the analysis.

Clearly, the estimation of the incidence of paediatric stroke can only be considered an underestimate, given that we do not yet know the coverage of our registry.

Another limitation is the lack of centralised review of imaging. This may result in missing or uncertain information regarding stroke aetiologies, particularly with regard to the classification of possible vasculopathies (e.g., focal cerebral arteriopathy – FCA vs. childhood primary angiitis of the CNS - cPACNS).

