### Procedure

The PRiSMA paediatric stroke registry is a multicentric, observational cohort study. So far 17 hospitals treating paediatric stroke patients are participating and enrolling patients. Further 6 centres are in the process of contract and ethics approval. In the first step, the study covers Germany as well as Austria and the Netherlands. Further European and international collaborations are planned.

Patients are recruited to the registry by the treating clinician at each study centre who obtains signed informed consent. Clear, age-appropriate informational materials are provided to the patient and their parents or legal representatives. Enrolment in the registry occurs only after obtaining a written informed consent form from the patient and their legal guardians. In accordance with data protection laws, a patient can withdraw his or her consent at any time.

If the patient and parents agree, they may be contacted by the coordinating study centre in Munich for a questionnaire-based survey on quality of life (QoL) and behaviour. A separate written informed consent is required for this component of PRiSMA.

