**Fig 1 pone.0341646.g001:**
[figure not shown]
Time points of data collection. **CBCL** – Child Behavior Checklist, **KINDL** – quality of life questionnaire, **QoL** – Quality of Life.

Data collection will be aligned with routine clinical appointments, to minimize research burden on families. If there is no doctor-patient contact on any of the proposed dates, no entry can be made in the registry. Data is entered into the database directly by the centres. An overview of collected data for both AIS or HS is shown in the Table 1.

**Table 1 pone.0341646.t001:** Overview of collected data of children with arterial ischemic stroke (AIS) or haemorrhagic stroke (HS) (categories, further details available on request).

CRF		
	**Data category**	**Details on**
**Acute**	Demographics	Age, sex, ethnicity, residence degree of urbanisation
	History of stroke event	Time of onset Clinical symptoms
	Medical history and previous development	Pre-existing conditions Development normal/with concerns
	Family history	Risk factors for stroke, cardiovascular/ thrombotic/ bleeding events in family members < 50 years of age
	Clinical examination at admission	GCS AWUP PedNIHSS Vital parameters (HR BP, temperature, ….)
	Neuroimaging (AIS)	Time of neuroimaging Modality (cCT, cMRI, cMRA,…) Results (incl. localization, affected vessel, results of vesselwall imaging, DWI/FLAIR mismatch, etc)
	Neuroimaging (HS)	Time of neuroimaging Modality (cCT, cMRI, cMRA,…) Bleeding volume (IVH: Graeb Score, SAH: Fisher Scale) Further specification: Aneurysm, AVM (Spetzler-Martin scale), cavernoma, dissection, angiopathy,…
	Diagnostic work up	Neurophysiology (i.e., EEG…) Cardiac work up (ECG, TTE, TEE) Laboratory testing (BC, vasculitis, coagulation, infectious, genetic testing)
	Acute Treatment (AIS)	Time of intervention Recanalization (thrombolysis, thrombectomy), antithrombotic treatment, immunosuppression etc.
	Acute Treatment (HS)	Time of intervention Interventional neuroradiology Neurosurgery
	Clinical course	Complications (arterial hypertension, seizures, increased intracranial pressure, infection)
	time of discharge clinical symptoms Treatment Follow up	Neurological examination, mRS Antithrombotic treatment, immunosuppression, ASM, other rehabilitation
	Stroke classification (AIS)	CASCADE criteria
	Stroke classification (HS)	ICH, IVH, SAH i.e., AVM, cavernoma, aneurysm, tumor, hypertension, medication induced, coagulation disorder, other
**Follow-up**	Demographics	Age at follow up

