## Outlook

To minimise loss to follow-up, we are developing a minimal data set questionnaire, which will be sent to families alongside the QoL questionnaires. This will enable us to obtain basic information regarding therapy and diagnostics even if children and adolescents no longer have regular medical appointments or have moved to predominantly outpatient care, for which no entries are made in the register after some time.

Further satellite studies are planned, including investigations into the genetic predisposition to childhood stroke.

We also plan to capture data about spinal stroke via PRiSMA which are even rarer than cerebral infarcts in childhood and adolescence. They can cause permanent damage to the spinal cord and lead to long-term disabilities [24–26]. Currently, there are limited published data on spinal infarcts in this age group, and no systematic long-term surveys have been conducted.

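### Clinic-rated function, and events away from participating centres, go unrecorded once a child leaves clinic follow-up, and the planned mailed form is not described as collecting them

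*Protocol article*

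**What the plan says.** All references are to the protocol article.

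- **Main outcomes** (Statistical analysis): mortality, recurrence, quality of life (KINDL), behaviour (CBCL), and neurological function (mRS, GMFCS, MACS and similar).
- **Source of function** (Data collection, Table 1): these scales belong to the follow-up form that the centre completes at a routine visit. The text under Fig 1 adds: "If there is no doctor-patient contact on any of the proposed dates, no entry can be made in the registry".
- **Source of KINDL and CBCL** (Data on Quality of Life and behavior): by mail, whether or not the child still attends. The stated advantage is less loss to follow-up, "as all patients and families will continue to be contacted even if they no longer attend or plan to attend medical appointments".
- **Consent for the mailing** (Procedure): "A separate written informed consent is required for this component of PRiSMA". The Organization section says of the coordinating centre that "it collects quality of life data directly from families who have given their consent".
- **Planned supplement** (Outlook): a minimal data set questionnaire, still in development, will go out together with the quality-of-life questionnaires. Its purpose is described thus: "This will enable us to obtain basic information regarding therapy and diagnostics even if children and adolescents no longer have regular medical appointments".
- **Missing data**: the Limitations section lists three steps, namely routinely collected items, then queries, then imputation: "Finally, multiple imputation techniques will be used to address any remaining missing data in the analysis". The Statistical analysis section is more cautious: "If necessary, multiple imputation procedures for missing values have to be used".

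**The concern.** The first two steps against missing data, routine items and queries, help when a visit took place and a field was left blank. They cannot recover a visit that never happened. For clinic-rated function in a child who no longer attends, the only step left on that list is imputation.

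Imputation in its usual form assumes that, given the recorded data, attendance is unrelated to the unseen outcome. Whether a child stays in specialist follow-up could well be related to how the child is doing. If so, the long-term distribution of function, and the prognostic models built on it, would carry a bias that imputation only partly removes. Events raise a related problem: a recurrence or death that no participating centre sees would appear as event-free or censored time in the planned Kaplan-Meier and cumulative incidence curves.

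The supplement meant to limit loss to follow-up is the natural place to collect these outcomes from families directly. As described, it is aimed at other content, and it appears to reach fewer families than the text on the mailing suggests.

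**Working it through.** **Step 1. Each main outcome against its source.** The article gives no figure for dropout, second consent or questionnaire response, so there is no stated figure to reproduce.

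| Main outcome | Where it is recorded | If the child has no clinic contact | Named in the minimal questionnaire? |
|---|---|---|---|
| mRS, GMFCS, MACS | Follow-up form at the centre | No entry | No |
| Recurrence | Own form at a participating centre, linkable across centres | Missed if treated elsewhere | No |
| Mortality | Through participating centres, as far as described | Can be missed | No |
| KINDL, CBCL | Mail, with separate consent | Still collected | Not needed, same mailing |

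**Step 2. What imputation can and cannot do.** All rates here are assumed. Let p = 60% be the true share with a good outcome, and a_g and a_p the attendance of children with good and poor outcome.

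Attenders only: p·a_g / (p·a_g + (1−p)·a_p).

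Imputation under missing at random: the same ratio within two equal strata of recorded baseline severity, then averaged. A weak predictor has a good outcome in 75% (mild) and 45% (severe). A strong one has 90% and 30%. Both average to 60%.

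Worked case, a_g = 0.7 and a_p = 0.9:
- Attenders only: 0.42 / (0.42 + 0.36) = 53.8%.
- Weak predictor: 0.525/0.75 = 70.0% and 0.315/0.81 = 38.9%, mean 54.4%.
- Strong predictor: 0.63/0.72 = 87.5% and 0.21/0.84 = 25.0%, mean 56.25%.

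| Attendance, good / poor | Attenders only | Imputed, weak predictor | Imputed, strong predictor |
|---|---|---|---|
| 80% / 90% | 57.1% | 57.4% | 58.2% |
| 70% / 90% | 53.8% | 54.4% | 56.25% |
| 50% / 90% | 45.5% | 46.9% | 51.3% |
| 80% / 60% (reversed) | 66.7% | 66.1% | 64.3% |

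If attendance depends only on recorded severity (50% of mild and 90% of severe cases attend):
- Attenders only, weak predictor: (0.5·0.5·0.75 + 0.5·0.9·0.45) / (0.5·0.5 + 0.5·0.9) = 0.39/0.70 = 55.7%.
- Attenders only, strong predictor: 0.36/0.70 = 51.4%.
- Imputation: 60% in both cases, the true value.

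So imputation removes all of the bias when attendance depends on recorded data, and only part of it when attendance depends on the unseen outcome. The sign follows whichever group attends less.

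**Step 3. Reach of the mailing among children who no longer attend.** Reach = share with second consent × share responding. With assumed values it runs from 50% × 50% = 25% to 90% × 70% = 63%. It equals all families only if both shares are 100%.

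**The case against.** Several stronger readings are tempting, and the documents do not support them.

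- *Recovered children are the ones who leave, so disability will be overstated.* The Outlook section mentions the end of regular appointments and a move to mainly outpatient care. It does not mention recovery. The reversed row in the table shows that the bias could go the other way.
- *The mailing asks nothing about outcomes.* It carries KINDL and CBCL, both main outcomes. The gap concerns only the outlined content of the minimal questionnaire, which is unfinished.
- *Function after death, or CBCL below its age range, will be imputed.* This is a strained reading. The plan treats death as a competing event and describes the CBCL from preschool age, and a value that does not apply is not a missing one.
- *The imputation model and sensitivity analyses are absent.* These commonly sit in an analysis plan, which is not shown, so their absence is no finding. The registry also records strong candidate predictors: PedNIHSS, discharge mRS and earlier follow-up mRS.

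Two further objections reduce the point. Recurrence has its own form and cross-centre linkage, so it does not depend on scheduled visits alone. The sentence about contacting everyone is limited to the quality-of-life part of the study, and the consent condition is stated openly elsewhere, so this is loose wording rather than a concealed restriction.

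None of this gives function a source once visits stop, or puts vital status, recurrence or function into the described content of the form.

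**Conclusion.** The point holds in a narrow form. Clinic-rated function has no registry entry without a doctor-patient contact, and a recurrence or death outside participating centres can be missed. The planned questionnaire is described as covering therapy and diagnostics. That it reaches only families with the separate consent is an inference from its being sent with the quality-of-life mailing. On that reading, the claim that all patients and families continue to be contacted overstates the mailing's reach.

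The size of any bias cannot be derived from the documents. In the illustration, the imputed share differs from the true 60% by between −13.1 points (46.9%) and +6.1 points (66.1%), and by nothing if attendance depends only on recorded data. These figures rest entirely on assumed attendance rates and predictor strength. They show that imputation alone is no guarantee; they do not show that the registry's results will be biased.

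The point deserves action because the remedy is collection rather than modelling, and the form is not yet final. With 31 patients enrolled by 17 Nov 25 and annual follow-up to adulthood, most of the follow-up still lies ahead.

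**What to change.** 1. While the minimal data set questionnaire is in development, add three items: vital status, recurrence with its date, and a parent-reported function or recovery question. The subjective full-recovery item in Table 1 can be reused.
2. Use these answers in the analysis of children without clinic follow-up, including as inputs to any imputation of clinic-rated function.
3. In the section on quality of life and behaviour, state that continued contact applies to all families who gave the additional consent, so that it agrees with the Procedure and Organization sections.

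The cost is a slightly longer form, and function that is reported by parents rather than rated by clinicians, so the two should be kept distinguishable in the analysis.

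Sending the form to every enrolled family under the main registry consent would extend its reach, but this is optional. Contact by the coordinating centre currently rests on the family's agreement (Procedure), and the database keeps only a non-reversible pseudonym (Data management). The extension may therefore need changes to contact-data and data-protection arrangements, and is not clearly cheap.
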